## Abstract

**Background:**

Aneurysmal subarachnoid hemorrhage (aSAH) is a neurological emergency, affecting a younger population than individuals experiencing an ischemic stroke; aSAH is associated with a high risk of mortality and permanent disability. The noble gas xenon has been shown to possess neuroprotective properties as demonstrated in numerous preclinical animal studies. In addition, a recent study demonstrated that xenon could attenuate a white matter injury after out-of-hospital cardiac arrest.

**Methods:**

The study is a prospective, multicenter phase II clinical drug trial. The study design is a single-blind, prospective superiority randomized two-armed parallel follow-up study. The primary objective of the study is to explore the potential neuroprotective effects of inhaled xenon, when administered within 6 h after the onset of symptoms of aSAH. The primary endpoint is the extent of the global white matter injury assessed with magnetic resonance diffusion tensor imaging of the brain.

**Discussion:**

Despite improvements in medical technology and advancements in medical science, aSAH mortality and disability rates have remained nearly unchanged for the past 10 years. Therefore, new neuroprotective strategies to attenuate the early and delayed brain injuries after aSAH are needed to reduce morbidity and mortality.

**Trial registration:**

ClinicalTrials.gov NCT04696523. Registered on 6 January 2021.

EudraCT, EudraCT Number: 2019-001542-17. Registered on 8 July 2020.

## Administrative information

Note: the numbers in curly brackets in this protocol refer to SPIRIT checklist item numbers. The order of the items has been modified to group similar items (see http://www.equator-network.org/reporting-guidelines/spirit-2013-statement-defining-standard-protocol-items-for-clinical-trials/).

## Introduction

### Background and rationale {6a}

Aneurysmal subarachnoid hemorrhage (aSAH) is a neurological emergency which is associated with a high risk of mortality and permanent disability. Subarachnoid hemorrhages account for approximately 5–10% of all strokes; however, the case mortality rate of aSAH at 1 year is considerably higher (50%) when compared to ischemic stroke. Up to 10–15% of patients with aSAH die before reaching the hospital [1–7]. In addition to mortality, aSAH is associated with a substantial impairment in the quality of life, with significant neurological deficits and psychological sequelae. About one in five survivors of aSAH will not regain functional independence and only every fourth regains the same level of functionality as before the aSAH [1–6]. In worldwide estimates, when compared with ischemic strokes, aSAH patients are disproportionately younger, i.e., of working age with the age at insult mostly below 66 years. In Finland, the mean age of the event is as young as 55 years [8]. Subsequently, aSAH is associated with a considerable loss of independent functionality and responsible for the development of dependency early in life. Novel treatments are needed to mitigate the effects of aSAH both in the immediate aftermath (early brain injury, EBI) and thereafter to improve the current dismal outcomes.

EBI is a major cause of mortality in aSAH patients [9–11]; it is defined as the period within the first 72 h after the ictus and describes the immediate overall brain injury after the aSAH. The initial clinical severity of the aSAH is the most important factor determining the overall outcome; this is assessed by a preliminary assessment of radiographic findings and neurological consciousness using the Glasgow Coma Scale (GCS), together with Hunt-Hess or WFNS grading. Initial radiographic markers of EBI (e.g., cytotoxic edema) are significant predictors of secondary complications and outcomes [9–11]. The pathophysiological disturbances underlying the radiographic findings during the EBI period are not completely understood; however, acute global ischemia, ischemia/reperfusion injury from the transient circulatory arrest at ictus, increased intracranial pressure (ICP), decrease in cerebral blood flow (CBF), and perfusion pressure (CPP) are clinically relevant pathological processes which can result in neuronal death. In addition, other pathophysiological mechanisms during the EBI period include disruptions of the blood-brain barrier, brain swelling, vasogenic and cytotoxic edema, acute vasospasm, dysfunction of autoregulation, altered ionic homeostasis, disruption of vascular integrity, excitotoxicity (e.g., via glutamate-activated receptors), thrombin activation, oxidative stress, inflammation (via activation of microglial cells), increased levels of matrix metalloproteinase (MMP) 9, and activation of the nitric oxide synthase (NOS) pathway. It has been suggested that there may be a causal relationship between delayed cerebral ischemia (DCI) and the severity of EBI. Therefore, an implementation of new treatment modalities targeting EBI seems to represent a promising avenue to attenuate its secondary injuries such as DCI and cerebral infarction [9–11].

Even after successful microsurgical or endovascular treatment of the ruptured aneurysm, DCI is still a potentially devastating clinical syndrome related to aSAH and it is the most significant cause for morbidity and mortality in patients who survive the initial aSAH [1–3, 12]. DCI is a clinical syndrome of focal neurological and cognitive deficits presenting in about 30% of aSAH patients at 3–14 days after the initial insult, which might progress to infarction [1–5, 12]. While an angiographically evident vasospasm in the cerebral arteries can be detected in 70% of patients, less than half of them develop any symptoms or ischemia in the territory supplied by the narrowed artery [1]. In addition, treatment with the calcium-channel blocker, nimodipine, which is currently the standard of care and the only pharmacological intervention that has been shown to reduce the risk of DCI and improve neurologic outcome by one-third after aSAH, does not alter the incidence or severity of delayed cerebral artery vasospasm [13]. Furthermore, other clinical trials involving drugs that exert a significant impact on vasospasm did not have any impact on the risk of DCI or outcomes [1, 12, 14]. Consequently, recent research has questioned whether there is truly a direct causal relationship between cerebral vasospasm and DCI and it has been suggested that DCI following an aSAH is actually the result of a variety of different pathophysiological mechanisms, which are currently incompletely understood [1, 12, 15, 16]. From preclinical and clinical studies, a number of possible mechanisms other than vasospasm to explain the link between DCI and infarction have been proposed including microthromboembolism, cortical spreading depolarization and ischemia, microcirculatory dysfunction, inflammation, and impaired cerebral autoregulation [12]. It has been recommended that the main outcomes of clinical trials investigating strategies to prevent DCI should measure the extent of cerebral infarction by either radiologic imaging or autopsy biopsy as well as the patient’s functional outcome [17].

The anesthetic properties of the noble gas xenon have been recognized since the late 1940s. Xenon is a near-perfect anesthetic gas as it is not metabolized, it is remarkably safe and efficient, has a minimal effect on hemodynamics, rapidly crossing the blood-brain barrier, as well as possessing very rapid induction and recovery characteristics due to its extremely low solubility (blood/gas partition coefficient of 0.115) [18, 19]. After the pivotal discovery that xenon is a non-competitive antagonist of the N-methyl-D-aspartate (NMDA) subtype of the glutamate receptor, numerous preclinical studies in three different species of animals and in various models of acute neuronal injury have confirmed that xenon confers neuroprotection [20]. There are many experimental models in which the beneficial effects of xenon have been evident, e.g., administration of excitotoxins or oxygen deprivation in rats [21–23], cardiopulmonary bypass (CBP) in rats [24], middle cerebral artery occlusion in mice [25, 26], cardiac arrest in pigs [27, 28], hypoxic-ischemic insult in rats [29, 30], TBI in mice [31–33], and SAH in rats. Neuroprotection has been demonstrated by a reduction in the infarct volume after focal ischemia [25, 26], attenuated short- and long-term neurologic and neurocognitive dysfunction [27, 28, 34–37], and a reduction in the extent of the neurohistopathological damage [20, 29, 31–37]. The neuroprotective properties of xenon were most clearly evident when the gas was administered either immediately or 2–6 h after injury [20, 30–37]. In addition to animal studies, the effect of xenon has been studied in humans mostly due to its cardioprotective properties. The potential cardioprotective properties of xenon anesthesia have been at least partly attributed to xenon’s ability to preserve cardiovascular stability by maintaining (i) systolic blood pressure, (ii) myocardial contractility, (iii) stroke volume, and (iv) preload, accompanied by an inotrope-sparing effect [38–40]. In addition, multiple molecular targets have been identified as being implicated in xenon’s cardioprotective conditioning effect. Phosphorylation of protein kinase cƐ, protein kinase B, and glycogen synthase kinase 3 β by xenon has been reported to inhibit the Ca2+-induced opening of transition pores in mitochondria, a process known to preserve mitochondrial function and prevent ischemic reperfusion injury and cell death [41]. Xenon’s potential cardioprotective properties were supported by the outcomes of Xe-Hypotheca trial; inhaled xenon reduced myocardial injury, as demonstrated by the significantly lower release of troponin-T from baseline to 72 h after cardiac arrest in the xenon-treated group as compared with the control group [40]. In a multicenter study on coronary artery bypass patients, the troponin I levels in the group who received xenon were significantly lower than the corresponding values in the sevoflurane group [42].

In 2016, we reported (Xe-HYPOTHECA trial; Clinicaltrials.gov NCT00879892) that xenon was able to attenuate the white matter injury after global ischemia after cardiac arrest [43]. The effect was mainly due to less extensive myelin damage in the xenon-treated group than in the control group. This was demonstrated by a significantly higher global fractional anisotropy of diffusion tensor imaging of white matter tracts in the xenon-treated patients than in the control patients [43]. The proper function of white matter is fundamental for good neurocognitive performance. Nonetheless, the Xe-HypotheCA trial was not powered to assess the clinical outcome. For example, the 6-month mortality was 15/55 (27.7 %) in the xenon-treated group and 19/55 (34.5 %) in the control group (adjusted HR 0.49 [95% CI 0.23–1.01], *P*=0.053). The interpretation of the authors was that this result was due to a combination of xenon’s neuro-and cardioprotective properties, which may also be clinically beneficial after aSAH.

Despite improvements in medical technology and advances in medical science, aSAH mortality and disability rates have remained virtually the same during the past 10 years [7]. The age and illness severity adjusted in-hospital mortality of 25–30% has also not changed over a span of 12 years, from 2003 to 2015 [5, 6]. Therefore, it is clear that new neuroprotective strategies are needed to attenuate the early and delayed brain injury occurring after an aSAH in order to improve the current dismal situation.

#### Objectives {7}

##### ***Hypothesis***

The primary hypothesis of the study is that the global white matter injury would be less severe as demonstrated with higher fractional anisotropy of DTI (diffusor tensor imaging) on the 1st MRI in patients treated with xenon, as compared to the patients who did not receive xenon.

#### Objectives

The primary objective is:

To explore whether xenon is neuroprotective in aSAH patients.

The secondary objectives are to explore the neuroprotective effects of xenon on:

The white matter injury in the cerebellum and corpus callosum. Recent studies have revealed that fractional anisotropy of white matter at 72 h post-SAH measured globally, in the cerebellum and in the corpus callosum, had an independent predictive value for both DCI and for a poor neurological outcome (i.e., mRS 3-6) [44].The incidence and severity of EBI within 72 h after the appearance of SAH symptoms, DCI, and cerebral infarction (according to a consensus statement [17] and consensus guidelines [5]: (1) DCI is defined as a new focal neurological deficit (such as hemiparesis, aphasia, apraxia, hemianopia, or neglect) or a decrease of at least 2 points in the Glasgow Coma Scale (either in the total score or in one of its individual components). This should last for at least 1 h and not be due to other causes (e.g., hydrocephalus, seizures, metabolic derangement, infection, sedation). DCI is not apparent immediately after aneurysm occlusion and cannot be attributed to other causes by means of clinical assessment, CT or MRI scanning of the brain, and appropriate laboratory studies; (2) cerebral infarction is defined as a new infarct on follow-up imaging (i.e., in any of the following: 2nd MRI, CT, CTA, DSA, and perfusion CT) between day 4 and 6 weeks after the initial appearance of SAH symptoms.The incidence of adverse events, serious adverse events, suspected unexpected serious adverse reactionsThe inflammatory process, i.e., assessed by the extent of microglial activation and the levels of cytokine in cerebral spinal fluid (CSF)The need and duration of intracerebral pressure (ICP) treatmentsPlasma catecholamine levelsThe release of troponin TThe release of neuron-specific enolase (NSE), neurofilament light (NF-L), glial fibrillary acidic protein (GFAP), calcium-binding protein S100B (S100B), ubiquitin carboxyterminal hydrolase L1 (UCH-L1), total tau, and cytokines (tumor necrosis factor alpha, interleukins 6 and 10)

The exploratory objectives are:

To explore the predictive value of the different MRI techniques (see details under the section of “Data collection and management”) alone and combined for clinical outcome at 3 months, and also at 1 and 2 years after SAH.To examine the pathophysiological pathways of the post-SAH period between the two treatment groups and to assess the predictive value of selected proteomics and metabolomics on severity of EBI and DCI and neurological outcome (i.e., good outcome: mRS 0–2 vs poor outcome: 3–6)To evaluate the role of microglial activation (see details under the section of “Data collection and management”) on the development of DCI.To explore the role of the cytokine level on the development of DCITo assess a combination of selected brain imaging markers obtained from different MRI techniques (see details under the section of “Data collection and management”), biomarkers (see secondary objectives # 8), plasma metabolomics (see details under the section of “Data collection and management”), CSF metabolomics and clinical examinations (e.g., motor score, pupillary light reflex with pupillometry, epileptic seizures) as a prognostication model for EBI, DCI, and neurological outcome at 3 months, at 1 and 2 years after SAH (i.e., good outcome: mRS 0–2 vs poor outcome: 3–6).To test the applicability of utilizing a brain network analysis with graph theoretical analysis and anatomical connectivity of white matter tracts (see details under the section of “Data collection and management”) in prognostic models for EBI, DCI, and neurological outcome at 3 months, at 1 and 2 years after SAH (i.e., good outcome: mRS 0–2 vs poor outcome: 3–6) and to investigate xenon’s effect on the connectivity.To unravel the mechanisms underpinning the development of EBI and DCI by utilizing brain imaging obtained from different MRI techniques (see details under the section of “Data collection and management”) and metabolomics (i.e., plasma and spinal fluid; see details under the section of “Data collection and Management”)To measure the clinical neurological outcome at 3 months and at 1 year and at 2 years.To develop a prognostication model for EBI and DCI and neurological outcome at 3 months and at 1 year and at 2 years after SAH

### Trial design {8}

The Xe-SAH study is a prospective, multicenter phase II drug intervention trial. The study design is a single-blind, prospective superiority randomized two-armed parallel follow-up study. The primary objective of the study is to explore the potential neuroprotective effects of xenon, when administered within 6 h of the initial insult, in adult (≥ 18 years of age), mechanically ventilated aSAH patients with a Hunt-Hess grading of 3–5. There are two study arms: the control arm receiving the current standard of care while the intervention arm will be administered a 24-h xenon treatment in addition to the standard care.

## Methods: participants, interventions, and outcomes

### Study setting {9}

Three university hospitals across Finland will participate in this study. The participating hospitals are Turku University Hospital, Tampere University Hospital, and Kuopio University Hospital. All patients with a new aSAH, admitted to the emergency room of each of the participating hospitals, will be screened for eligibility to be included in this trial.

### Eligibility criteria {10}

The inclusion criteria are:

Informed consent obtained from the next of kin or legal representativeAneurysmal subarachnoid hemorrhage visible on CT, CTA, or DSAHunt-Hess grading of 3–5Age of ≥ 18 yearsThe patient has been intubatedGCS 3–12 obtained off neuromuscular blocking agentsXenon treatment can be initiated within 6 h after the onset of aSAH symptoms

The exclusion criteria are:

Acute traumatic brain injuryMaximum diameter of intracerebral hemorrhage > 2.5 cmPneumothorax or pneumomediastinumAcute lung injury requiring ≥ 60% Fi02 (fraction of inspired oxygen)Systolic arterial pressure < 80 mmHg or mean arterial pressure < 60mmHg for over a 30-min periodBilaterally fixed and dilated pupilsPositive pregnancy test, known pregnancy, or currently breast-feedingChronic neurological deficiency due to chronic traumatic brain injury or other neurological illnessImminent death or current life-threatening diseaseCurrent enrollment in another interventional studyThe subject is known to have a clinically significant laboratory abnormality, medical condition, or social circumstance that, in the investigator’s opinion, makes it inappropriate for him/her to participate in this clinical trialPresence of implants or foreign bodies which are not known to be MRI safe

#### Who will take informed consent? {26a}

In this study, eligible patients are comatose and in an immediate life-threatening condition. In addition, it is likely that xenon’s putative neuroprotective effect can be achieved only if xenon inhalation has been started within 6 h after onset of SAH symptoms. Therefore, obtaining a written informed consent from next of kin or a legal representative is highly time-sensitive. An alert of an incoming SAH patient will be distributed to the study physicians (on-call anesthesiologists, intensivists, and neurosurgeons) via the phone to come to the ED to allow recruitment to proceed. The patient’s next of kin will be informed of the study either in-person or by remote communication, and written consent will be obtained either in person or electronically. A written consent will also be obtained from all those patients, who will regain full legal capacity after a sufficient neurological recovery.

#### Additional consent provisions for collection and use of participant data and biological specimens {26b}

Information that characterizes the participant’s condition prior to the initiation of experimental treatment will be obtained as soon as clinically reasonable. These include knowledge of the participant’s demographics, medical history, vital signs, and oxygen saturation. The written consent includes permission to collect blood samples, spinal fluid, and radiologic image data.

The collected information will contain quantitative and qualitative data of the patients, as stated in recent recommendations issued by the working group on subject characteristics, and will include all relevant Common Data Elements (CDE) (138). Specific definitions, measurements tools, and references regarding each SAH CDE can be found on the weblink here: https://www.commondataelements.ninds.nih.gov/sites/nindscde/files/Doc/Stroke/CDEStartupResource_Stroke.pdf.

Surgical interventions, additional detailed information related to SAH (i.e., CDE), changes in clinical status, all routinely monitored signs (i.e., arterial blood pressure, heart rate, intracerebral pressure), collected laboratory tests, and concurrent medical therapy given to the patient during the ICU stay will be recorded. GCS score, concomitant medications, surgical interventions, and neurologic conditions are collected daily during the hospitalization.

This clinical study protocol adheres to the SPIRIT reporting guidelines [45].

## Interventions

### Explanation for the choice of comparators {6b}

Despite improvements in medical technology and advances in medical science, aSAH mortality and disability rates have remained virtually the same during the past 10 years [7]. The standard of care in Finland for aSAH follows the standardized best practice guidelines set out by the American Heart Association and the American Stroke Association [46] and is the gold standard and in everyday use in the hospitals at which this trial will be conducted. The standard state-of-the-art care is therefore justified as the comparator for which this study seeks to find an improvement.

### Intervention description {11a}

After successful recruitment into the study, the patients will be randomized into one of two arms:

The first arm is the current standard of care accompanied with normothermia (i.e., 36.5–37.5 °C).The second arm is the xenon intervention group, where the participants will receive inhaled xenon for 24 h with an end-tidal concentration of 50 ± 2% and normothermia (i.e., 36.5–37.5 °C) and the standard of care thereafter.

The intervention arm will receive xenon administered at 50 ± 2% in oxygen for 24 h upon admission to the intensive care unit. The concentration of xenon administered will be monitored at both the inspiratory and expiratory limbs of the rebreathing circuit using a thermoconductivity analyzer, which is automatically calibrated when the delivery system is initiated. If the concentration of xenon administered drops below 45%, the system will be flushed to displace any nitrogen emerging from blood and tissues into the closed-circuit system. Flushing will be continued until a xenon concentration of at least a 50% is reached. Xenon will be administered for 24 h through the rebreathing circuit. If the patient should require surgery for any reason during the xenon inhalation treatment, the procedure will be performed under xenon anesthesia whenever feasible. Supplemental sedative, anesthetic, and pain medication are to be provided as necessary during surgery. A failure to maintain a 50% concentration of xenon in oxygen during the treatment phase is not a reason to disqualify the patient from the study. In such a case, the treatment will be continued with the safest concentration that can be administered. The end-tidal xenon concentration of 70% may not be exceeded nor can it be less than 30% (i.e., the upper safety limit and lower efficacy limit of xenon concentration).

Since acute hydrocephalus is relatively common after aSAH, most of the recruited patients will receive an external ventricular drain. ICP monitoring will also be performed in all patients. ICP target is set to ≤ 20 mmHg; an optimal head position of 30° will be ensured. The ICP monitoring device must be in place prior to the commencement of xenon inhalation. Mechanical ventilation and adjustments will be made based on regular treatment. The inspiratory oxygen will be adjusted to maintain a partial pressure for arterial oxygen in the range of 12–20 kPa. Minute ventilation will be adjusted to maintain the partial pressure for arterial carbon dioxide in the range of 4.5–5.5. kPa. Repeated blood-gas analysis will be performed every hour during the xenon treatment, and later whenever indicated but at least every 4 h. The following hemodynamic targets are set: cerebral perfusion pressure (CPP) > 60mmHg, mean arterial pressure (MAP) > 65mmHg. Management of hemodynamics will be primarily achieved through the use of vasopressors (e.g., norepinephrine, epinephrine, dopamine, dobutamine), and antiarrhythmic medications will be administered as needed and according to local protocols. Hypertension will be treated with vasodilators.

Serum glucose-targets are set to between 5.0 and 10.0 mmol/L and hematocrit between 0.3 and 0.45. Potassium will be supplemented if the serum potassium level is < 4 mmol/L. Plasma sodium levels will be maintained above 135 mmol/l and will not be corrected if osmotic therapy for intracranial hypertension results in an elevation of plasma sodium, unless it exceeds 155 mmol/l. Normothermia of 36.5–37.5 °C will be maintained after ICU arrival. The core temperature will be managed with infusions of diclofenac and paracetamol according to clinical routine at each center.

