## Assignment of interventions: blinding

### Who will be blinded? {17a}

The physicians responsible for assessing the neurologic outcome as well as the neuroradiologist analyzing the brain imaging will be unaware of the treatment-arm. The immediate care-providers, including the attending physician and their team, cannot be blinded during the intervention phase, due to logistical and treatment effects related to xenon-administration.

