### Plans for collection, laboratory evaluation, and storage of biological specimens for genetic or molecular analysis in this trial/future use {33}

Biochemical assessment: A blood sample of 20 ml for determination of plasma catecholamines, plasma metabolomics (see details of metabolomics under the section “Data collection and management”), cardiac enzyme release (P-hs-troponin-T and heart fatty-acid binding protein), neuron-specific enolase (NSE), neurofilament light (NF-L), glial fibrillary acidic protein (GFAP), calcium-binding protein S100B (S100B), ubiquitin carboxyterminal hydrolase L1 (UCH-L1), total tau, and cytokines (tumor necrosis factor alpha, interleukins 6 and 10) will be analyzed at ICU arrival and at 24h, at 48h, and at 72h after onset of SAH symptoms; urine catecholamines during first and second 24 h. In addition, a sample of spinal fluid will be collected through EVD at ICU arrival or as soon as it is in place and at 24h, at 48h, and at 72h after onset of SAH symptoms for assessment of metabolomics. P-hsTn-T and P-NSE will be determined by a local university hospital laboratory with standard methods. The samples will be destroyed 10 years after completion of the study. In addition, the patient has a right to require destruction of the samples at any time. In this study, no tissue samples will be collected, and no genetic analysis are conducted.

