As a secondary endpoint of the Xe-HypotheCA trial, inhaled xenon combined with mild therapeutic hypothermia resulted in a reduced myocardial injury when compared to that achieved by hypothermia alone as demonstrated by the significantly lower release of troponin-T from baseline to 72 hours after OHCA in the xenon group. The incremental change of troponin-T was also associated with higher mortality at six months [40]. In addition, the Xe-Hypotheca trial revealed that inotropic support with norepinephrine during the first 72 h after cardiac arrest was 84.3% higher in the control group than in the patients treated with xenon. Among aSAH patients, 35% displayed elevations of troponin I, 35% experienced arrhythmias, and 25% exhibited ventricular wall motion abnormalities with a catecholamine-induced process proposed to be the most plausible mechanism behind the cardiac complications [5, 81–84]. It is known that the cardiac manifestations, which usually persist for 1–3 days, are more common in patients who will later develop DCI, and these are associated with worse outcomes. A clinical syndrome termed Neurogenic Stress Cardiomyopathy (“stunned myocardium”) may contribute to death in 12% of aSAH patients. It is also well-documented that high levels of catecholamines associate with cardiac dysfunction, late vasospasm, and poorer outcome [85–91]. Therefore, xenon’s cardioprotective and inotrope-sparing effects may prove to be beneficial after an aSAH.

The start of the trial has been postponed due to the respirator shortage caused by the corona pandemic, but it is now expected to start during 2023. Patient recruitment will start initially (i.e., a feasibility period of 3–6 months) in Turku University Hospital, with Tampere and Kuopio University Hospitals joining in at a later stage after the feasibility period. Patient recruitment is expected to last four (4) years and the neurological follow-up surveys will require an additional two (2) years. A feasibility study will be published, once 30 patients have successfully gone through the randomization process and received treatment. One of the main endpoints of the feasibility study is to demonstrate the safety of xenon when assessing ICP.

Due to the devastating nature of an aSAH, there is an urgent need for new neuroprotective strategies to reduce both the mortality and morbidity that are associated with aSAH. In this respect, this study aims to deliver new interventional strategies for the treatment of aSAH.

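### Plasma catecholamine level, a secondary outcome, is sampled while catecholamines may be infused, so a difference between arms cannot be read as endogenous release or neuroprotection

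*Protocol article*

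**What the plan says.** Section Objectives {7} lists plasma catecholamine levels among the measures on which xenon's neuroprotective effects are to be explored. Outcomes {12} repeats them as a secondary outcome, without separating endogenous from infused hormone. The section on biological specimens {33} says that the blood markers, catecholamines among them, "will be analyzed at ICU arrival and at 24h, at 48h, and at 72h after onset of SAH symptoms". It also collects "urine catecholamines during first and second 24 h", but urine levels appear in neither the objectives nor the outcome list, so they are a specimen and not a listed outcome.

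Intervention description {11a} sets targets of "cerebral perfusion pressure (CPP) > 60mmHg, mean arterial pressure (MAP) > 65mmHg" for all patients and says that hemodynamics are to be managed primarily "through the use of vasopressors (e.g., norepinephrine, epinephrine, dopamine, dobutamine". Section {17a} adds: "The immediate care-providers, including the attending physician and their team, cannot be blinded during the intervention phase".

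The Discussion reports that in the earlier xenon trial "inotropic support with norepinephrine during the first 72 h after cardiac arrest was 84.3% higher in the control group" than in the xenon group, and argues that xenon's cardioprotective and "inotrope-sparing effects may prove to be beneficial after an aSAH".

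Statistical methods {20a} adjusts for age, sex and site, with other baseline characteristics added when needed. Concurrent therapy in the ICU is recorded ({26b}, {18a}). Nothing in the article ties the infusion running at a blood draw to the catecholamine value from that draw.

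**The concern.** Norepinephrine, epinephrine and dopamine are the same molecules whether released by the patient or given by pump, and a plasma concentration does not show which. Dobutamine is synthetic and does not raise this problem.

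Infused drug would matter less if it were balanced between arms. The protocol gives its own reason to expect imbalance: it anticipates that xenon lowers inotrope need. In addition, treating staff are unblinded and the pressure targets are lower limits only, which leaves room for discretion above them.

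If the comparison is run as written, a lower plasma level in the xenon arm could be credited to xenon as protection when it reflects less infused drug. Adjustment for baseline variables cannot remove this, because the infusions are given after randomisation.

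**Working it through.** The plan gives no effect size, SD or power for this outcome. Its only sample-size calculation concerns global fractional anisotropy and does not bear on this point. The check has two parts.

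**1. Timing**
- Xenon must be startable within 6 h of onset ({10}) and runs for 24 h ({11a}). A full course therefore ends between 24 h and 6 + 24 = 30 h after onset.
- The arrival draw is close to baseline, because xenon starts on ICU admission.
- The 24 h draw falls during xenon or at its end.
- The 48 h draw comes 48 − 30 = 18 h to 48 − 24 = 24 h after xenon ends. The 72 h draw comes 42 to 48 h after.
- Vasopressors may be running at any of the four draws. The arm contrast in infused drug may differ from draw to draw.

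**2. Size of a purely infused difference**

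Notation: E is the endogenous level, assumed equal in both arms. I is the infused contribution in the xenon arm. s = I/(E + I) is the infused share of the xenon-arm level. d is the relative excess of infused drug in controls. Assume that the infused contribution is proportional to the drug given and that clearance is equal in both arms.

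Control/xenon ratio = [E + (1 + d)I] / (E + I) = 1 + d·s

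Inputs: d = 0.843 from the Discussion, for norepinephrine only. The documents do not give s, so it is varied.

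| s (assumed) | 1 + 0.843·s | Control level higher by |
|---|---|---|
| 0.10 | 1.08 | 8% |
| 0.25 | 1.21 | 21% |
| 0.50 | 1.42 | 42% |
| 0.75 | 1.63 | 63% |
| 0.90 | 1.76 | 76% |

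The result is equally sensitive to d. With half the excess (0.843/2 = 0.4215) and s = 0.50, the ratio is 1 + 0.4215 × 0.50 = 1.21 instead of 1.42. With d = 0 it is 1 for every s.

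So if controls receive more of a given catecholamine (d > 0, s > 0), its total level is higher in controls even when endogenous release is identical. The documents fix neither s nor d for this population, so the table is an illustration and not an estimate.

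**The case against.** **Less infused drug may be a real effect of xenon.** This stands. The Discussion presents inotrope-sparing as a property of xenon, and all patients share the same pressure targets. Total circulating catecholamine is then a legitimate outcome of the randomised policy. What it does not support is a statement about endogenous release or neuroprotection, and Objectives {7} lists the measure under neuroprotective effects.

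**The text never calls the outcome endogenous release.** Also true. The sympathetic mechanism in the outcome list belongs to the separate cardiomyopathy item. But with no definition in either direction, the neuroprotective label is the only interpretation the protocol supplies.

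**The handling may be in an analysis plan that is not shown.** Possible, and the infusion data will exist. The point here is narrower: the protocol itself fixes the outcome, its role as a measure of neuroprotection, and baseline-only covariates.

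**The 84.3% does not carry over.** Largely right. It comes from cardiac-arrest patients treated with hypothermia, whereas this trial uses normothermia after aSAH. It covers norepinephrine only, and it summarises 72 h of use rather than the moment of a draw.

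**A stronger reading is tempting:** that the result will mostly show how much drug unblinded staff chose to infuse. The documents do not support it. They give no proportion of patients infused, no doses and no endogenous levels, and nothing shows that staff discretion rather than hemodynamic need would drive a difference. Unblinding makes such a contribution possible, no more.

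**Conclusion.** The point holds as one of interpretation. As defined, plasma catecholamine level mixes endogenous and infused hormone, the protocol anticipates that the infused part will differ by arm, and the stated adjustment does not address this. A difference between arms cannot by itself be attributed to endogenous release or to neuroprotection.

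If xenon patients receive less infused catecholamine, the distortion makes xenon look better on this measure. Its size is unknown. The 8% to 76% range rests on assumed infused shares of 10% to 90%, equal endogenous levels, and an 84.3% excess borrowed from another population.

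One secondary outcome is affected. Urine catecholamines should not be counted as a second affected outcome.

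**What to change.** No change to treatment is needed.

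1. Define the outcome as total plasma level, endogenous plus infused, and state that no conclusion on sympathetic activation or neuroprotection will be drawn from it alone.
2. For each plasma draw, including the one at ICU arrival, link the name and rate of any catecholamine infusion from the ICU record.
3. Analyse norepinephrine, epinephrine and dopamine separately, in all randomised patients, with the ICU-arrival value as covariate.
4. Report cumulative vasopressor dose by arm alongside, so that an inotrope-sparing effect is visible as such.
5. Label any analysis limited to samples drawn without infusion of that species as a sensitivity analysis only. It conditions on something that happens after randomisation and that xenon may change. If controls are infused more often, more of them drop out and those left are likely the more stable ones. Adjusting the main comparison for infused dose is no remedy, for the same reason.

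The cost is a small data-linkage task, since concurrent therapy is already recorded, and a weaker permitted conclusion for this one secondary outcome.
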